#### Four-week rehabilitation program

##### Control group

The Control group participants will complete 4 weeks of the SPaR Program without a HEP.

##### Praxis group

An innovative rehabilitation program has been designed to enhance function by integrating therapeutic elements into a VR-based platform, referred to as the Praxis system. The components of the Praxis system include a laptop, VR headset and controller, 3D-printed replica M4 rifle, router, and ethernet cable. The hardware details are summarized in Table 1 and Figure 4. The Praxis group participants will receive 4 weeks of Praxis-delivered augmented vestibular rehabilitation, which will be overseen by an Occupational Therapist. Each session will last 45 min daily, 5 days a week, and will be supplemented with a personalized HEP using the VestAid device (12) for 20 min a day, 5 days a week. Progression is individualized; the Occupational Therapist will adjust visual/cognitive load, duration, and movement parameters (e.g., head velocity) based on patient performance and symptoms, allowing treatment to be tailored to evolving functional abilities. Daily ratings for specific VOMS symptoms (headache, dizziness, nausea, and fogginess) will be collected pre- and post-exercise, rated on a 0–10 scale, to monitor symptoms throughout the rehabilitation.

**Table 1 T1:** Praxis system components and specifications.

**Components**	**Specifications**
Alienware x17 R2 laptop and power adapter (Dell Technologies, Round Rock, TX)	Processor—12th Gen Intel Core i9-12900HK Graphics Card—NVIDIA RTX 3080 Ti RAM—32 GB
VIVE Focus 3 virtual reality headset with eye tracker and power adapter (HTC Corporation, Taiwan)	Virtual reality headset with eye tracker
VIVE Focus virtual reality controller and power adapter (HTC Corporation, Taiwan)	Only the right-hand controller is used in the replica M4 rifle
Replica M4 rifle (National Equipment Corporation (NECO), College Station, TX)	Approximate size and weight of a M4 Carbine rifle
Router and power adapter (NETGEAR, San Jose, CA)	NIGHTHAWK AX6 AX5400 6-Stream Wi-Fi router
Ethernet cable	Used to connect the laptop to the router

**Figure 4 F4:**
[figure not shown]
Praxis system components.

The Praxis-delivered augmented vestibular rehabilitation consists of three first-person-shooter serious games (Figures 5A–C). The Occupational Therapist can modify the visual complexity and cognitive demand of the games to adapt to patient needs. In Barricade Wave Defense (Figure 5A), patients shoot enemies from behind a barricade which requires them to move their heads and bodies. This game challenges attention, dynamic stability, agility, reaction time, gaze stability, and smooth pursuit. In Directional Memorization (Figure 5B), patients memorize direction orientation and then shoot enemies in response to directional cues. This game challenges spatial memory, attention, dynamic stability, gaze stability, and smooth pursuit. In Stroop Target Shoot (Figure 5C), patients memorize the location of colored drones and shoot those matching the color of the cue (vs. the named color). This game challenges spatial memory, attention, dynamic stability, response inhibition, reaction time, gaze stability, smooth pursuit, and saccades. The games provide a variety of outcome metrics, including response times, hit rates (accuracy), head velocity and rotation, and time on target (eye gaze).

**Figure 5 F5:**

Praxis consists of three first-person-shooter serious games: **(A)** Barricade Wave Defense, **(B)** Directional Memorization, and **(C)** Stroop Target Shoot.

#### Interim (weekly) assessments (Praxis group only)

At the end of each week, participants in the Praxis group will complete a GROC (30). They will also assess their current level of function on a scale from 0 to 100, with 100 representing optimal function (41).

#### Follow-up assessment

At the 4-week follow-up, all self-reported questionnaires (DHI, PSQI, GAD-7, PCL-M, VAAI-9, HIT-6, SBSOD, and fogginess rating) and the Readiness Assessment Battery (HAM-4-mTBI, modified version of the POWAR-TOTAL, 5-10-5 Shuttle Run, and 300-yard Shuttle Run) will be re-retested on all participants. The Praxis group will undergo another neurophysiological assessment (rs-fMRI) and will complete the SUS questionnaire (50) evaluating the Praxis system. Additionally, participants in the Praxis group will complete a final GROC (30) scale and reassess their current level of function on a scale from 0 to 100, with 100 representing optimal function (41).

#### Oura ring

Each participant will wear an Oura ring for the study duration. The Oura ring, equipped with a 3D accelerometer, will track activity levels and calculate daily energy expenditure using Metabolic Equivalents (METs). It will also monitor resting heart rate (an indicator of general health, wellness, and anxiety levels), heart rate variability (a potential marker of autonomic health, noting that some individuals show impairments following mTBI (51), which may improve post-rehabilitation), and the quantity and quality of sleep (sleep score, total sleep time, and wake-up time; as sleep is a key factor in recovery from mTBI (52)). Additionally, the activity score and inactive time will be recorded as markers of general health/wellness and to quantify activities conducted outside of the SPaR Program, which may act as confounding variables that need to be controlled for in statistical analyses.

The overall study procedures are reflected in Figure 6.

**Figure 6 F6:**
[figure not shown]
Schedule of data collection. GROC, Global Rating of Change; rs-fMRI, resting state functional magnetic resonance imaging.

### Statistical/data analysis plan

#### Sample size and justification

The sample size of *n* = 15 for the Praxis group was determined based on practical feasibility, alignment with similar neurophysiological assessment studies (4, 14, 53), and funding constraints. Increasing the sample size beyond 15 offers minimal benefit in reducing confidence interval ranges (54), which are crucial for precision in effect size calculations for future studies.

Before performing any statistical analyses, we will assess all relevant statistical assumptions (e.g., normality, homogeneity of variance) to ensure appropriate test selection and the validity of results. Additionally, corrections for multiple comparisons will be applied to control the false discovery rate and minimize the risk of Type I error.

#### Descriptive statistics

Descriptive statistics, including percentages, means, and standard deviations will be used to describe the demographic characteristics of the sample, such as age, sex, height, weight, BMI, MOS/AOC, time in service, number and duration of deployments, number of self-reported and clinician-confirmed mTBI incidents and their causes, support structure (e.g., single, married), history of migraines/headaches, history of attention deficit hyperactivity disorder and/or learning disorders, and medical/surgical history. Differences within the sample will be analyzed using the chi-square test for proportions. Continuous variables will be analyzed using analysis of variance (ANOVA). The Oura ring data will be summarized as daily averages for each metric (e.g., METs, resting heart rate, heart rate variability, sleep score) and used as covariates in statistical analyses to control for individual variations in physical activity, sleep quality, and autonomic function. These covariates will help isolate the effects of the rehabilitation program on functional outcomes.

#### Neuroimaging changes following Praxis treatment

The neuroimaging will involve structural (sMRI) and rs-fMRI data acquired from a Siemens 3T scanner (MAGNETOM Skyra Fit) at Brooke Army Medical Center. Key imaging parameters for sMRI are TR = 2,530 ms, TE = 2.6 ms, FA = 7o, FOV=256 mm × 256 mm, Matrix = 256 × 256, Sagittal Slices = 176, Thickness = 1 mm; and for rs-fMRI, TR = 2,130 ms, TE = 30 ms, FA = 85o, FOV=220 mm × 220 mm, Matrix = 64 × 64, Axial Slices = 39; Thickness = 3.4 mm, Measurement = 245.

Using our data analysis pipeline implemented with the “AFNI” software package (afni.nimh.nih.gov), the analysis at the individual level will go through eight processing steps of (i) outlier detection, (ii) despiking, (iii) slice timing correction, (iv) volume registration, (v) template normalization into the MNI space (55), (vi) image segmentation for gray matter, white matter, and cerebral spinal fluid (CSF), (vii) nuisance signal (head motion, white matter, and CSF) regression, and (viii) spatial smoothing (FWHM = 5 mm). Subsequently, the analysis of rs-fMRI will evaluate differences in the (i) FC (56), (ii) ReHo (57), and (iii) fALFF (58) between baseline and post-rehabilitation. While the ReHo and fALFF will be evaluated across the whole brain, FC will be evaluated in the vestibular visual network (59). Voxel-wise values of FC, ReHo, and fALFF will be derived individually, and linear-mixed-effect (LME) modeling (60) will be performed, using imaging times (pre- vs. post-rehabilitation) as the variable of interest and head motion as the covariate. The rehabilitation effect revealed by this analysis will be corrected for multiple comparison by a Monte Carlo simulation (61).

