##### Resting-state functional MRI (rs-fMRI; Praxis group only)

Only participants in the Praxis group will undergo this assessment. With a Siemens 3T scanner (MAGNETOM Skyra Fit), anatomical and functional scans will be performed during each MRI session, alongside localizer scans. The acquisition parameters will follow established guidelines and standard methodologies to ensure comparability with previous studies. To this end, the team will closely mimic published protocols (14, 49), with the anatomical acquisition for co-registration intended to use magnetization-prepared rapid acquisition gradient echo (MPRAGE) imaging. The functional echo-planar imaging (EPI) sequence parameters will be selected to closely align with those used in prior research (14), including a repetition time (TR)/time to echo (TE) of 2,130 ms/30 ms, a field of view (FoV) of 220 mm x 220 mm, a voxel size of 3.4 mm x 3.4 mm x 3.4 mm, an axial slice number of 39, and a volume count of 245, with an expected rs-fMRI scan time of ~8.7 min. The rs-fMRI outcomes include functional connectivity (FC), regional homogeneity (ReHo), and fALFF, which will be analyzed to assess neurophysiological changes post-rehabilitation.

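### Smoothing at 5 mm before ReHo is computed inflates ReHo and compresses its scale unevenly; ReHo should be computed first and its map smoothed afterwards

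*Protocol article*

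**What the plan says.** In *Neuroimaging changes following Praxis treatment*, the article states that "the analysis at the individual level will go through eight processing steps". The seventh step is nuisance regression. The eighth, and the sentence that follows it, read: "viii) spatial smoothing (FWHM = 5 mm). Subsequently, the analysis of rs-fMRI will evaluate differences in the (i) FC (56), (ii) ReHo (57", with fALFF as the third measure. Voxel-wise values of all three measures then enter a linear mixed-effects model comparing the scans before and after rehabilitation. ReHo and fALFF are examined across the whole brain.

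The section gives one stream for all three measures. Neither it nor *Resting-state functional MRI (rs-fMRI; Praxis group only)* says that ReHo is taken from unsmoothed data, or that smoothing is applied to the finished ReHo map.

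**The concern.** ReHo is a measure of local synchrony: the agreement between a voxel's time series and those of its immediate neighbours. Smoothing replaces each voxel's series by a weighted average over those neighbours, so it raises their agreement whether or not the tissue is synchronous. FC across a network and fALFF are not open to this objection, so one order does not suit all three measures.

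At stake is what a ReHo difference means. The imaging outcomes go on to the correlations with behaviour and to the mediation analysis, and the pilot is meant to lay the groundwork for larger trials. If the scale is inflated by an amount that depends on a region's starting level, raw differences cannot be compared between regions or carried forward as effect sizes in W.

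**Working it through.** **Inputs from the article.** "a voxel size of 3.4 mm x 3.4 mm x 3.4 mm"; "FOV=220 mm × 220 mm, Matrix = 64 × 64"; "a volume count of 245, with an expected rs-fMRI scan time of ~8.7 min"; TR 2,130 ms; kernel FWHM 5 mm.

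**Check of the stated figures.** 245 × 2.130 s / 60 = 8.70 min, and 220 / 64 = 3.44 mm. Both agree with the text. The article gives no ReHo value to reproduce.

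**Assumptions.** ReHo is Kendall's W over 27 voxels. Voxel noise is spatially white, with a shared local signal giving every pair of voxels correlation rho. Rho is not in the article, so it is varied.

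**Kernel.** Sigma = 5 / 2.355 = 2.12 mm. Noise in two face-adjacent voxels, independent before smoothing, then has correlation exp(−3.4² / (4 × 2.12²)) = 0.53.

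**Kendall's W.** With K = 27, W = (1 + 26 × mean Spearman) / 27 and Spearman = (6/π) arcsin(r/2). Unsmoothed, r = rho. Smoothed, r = (rho + (1 − rho)c) / (rho + (1 − rho)v), where v is the noise variance left after smoothing and c is the smoothed noise covariance of the pair. The kernel's share is (W smoothed − W unsmoothed) / W smoothed.

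Results at 3.4 mm:

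| rho | W unsmoothed | W smoothed | kernel's share | change in W for +0.05 rho, unsmoothed | same, smoothed |
|---|---|---|---|---|---|
| 0 | 0.037 | 0.175 | 79% | 0.046 | 0.266 |
| 0.1 | 0.129 | 0.587 | 78% | 0.046 | 0.093 |
| 0.2 | 0.221 | 0.745 | 70% | 0.046 | 0.047 |
| 0.4 | 0.407 | 0.880 | 54% | 0.047 | 0.019 |
| 0.5 | 0.502 | 0.916 | 45% | 0.048 | 0.014 |
| 0.6 | 0.597 | 0.942 | 37% | 0.048 | 0.010 |

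For example, at rho 0.4 the share is (0.880 − 0.407) / 0.880 = 54%. Without smoothing, the response to a given change in rho is almost constant. With smoothing first, it falls from 0.266 to 0.010 across the table. Simulation gives matching values: noise 0.038 to 0.18, and rho 0.4 from 0.405 to 0.88.

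**Sensitivity.** The output grid of template normalization is not stated. On a 3.0 mm grid, noise-only W rises to 0.24 and the response at rho 0.4 is 0.013. On a 2.0 mm grid these are 0.46 and 0.003. With 7 neighbours at 3.4 mm, noise-only W rises from 0.14 to 0.37.

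**Effect on the contrast.** In simulations with signal in a 5 × 5 × 5 cube, the difference at the centre divided by its run-to-run spread was 4.7 as planned against 4.9 with the map smoothed afterwards (rho 0.10 to 0.15), and 2.0 against 2.3 (rho 0.40 to 0.45).

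**Location.** In the same model, the difference at the edge of the cube relative to the centre was 0.57 as planned against 0.48 at low rho. At rho 0.4 it was 0.94 to 0.99 against about 0.50, so the change spreads about one voxel further.

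**The case against.** Four points can be made on the other side.

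- **The planned inference is a contrast.** Only the Praxis group is scanned, each person is compared with themselves, and nothing sets ReHo against a norm. The kernel is the same at both scans. This stands: a reader might infer a spurious rehabilitation effect or a material loss of power, and neither follows. W still rises with true synchrony, and the standardised contrast barely moves because its spread shrinks along with the difference.
- **The size depends on an assumed rho.** A reader might infer that ReHo as planned is mostly an artefact of the kernel. The article gives no local correlation to support that. In this model the kernel's share exceeds half only up to rho of about 0.4, and scanner smoothness and interpolation during normalization are not modelled. The pure-noise figure is the extreme case. This stands.
- **The article may condense a measure-specific order.** That is possible, and the cited ReHo method paper is not shown. But the text does not leave the order open: it numbers the steps and places ReHo after the last one. The sentence needs changing either way.
- **Comparability with earlier work.** A reader might infer that the plan breaks its own promise, since the MRI section says "The acquisition parameters will follow established guidelines and standard methodologies to ensure comparability with previous studies". That sentence concerns scanner settings and promises nothing about processing order or the ReHo scale, so it lends the point no support.

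**Conclusion.** The point holds, at minor severity. As written, ReHo is computed from smoothed time series. In the model at 3.4 mm this raises W from about 0.04 to 0.18 on noise and from 0.41 to 0.88 at rho 0.4. The same true change of 0.05 in rho appears as about 0.09 to 0.10 in W at rho 0.1 and 0.02 at rho 0.4, where unsmoothed input gives about 0.047 at both. What suffers is the interpretation of raw ReHo size and, at moderate rho, of location by about one voxel. The validity of the pre-post test does not suffer.

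These figures rest on white voxel noise, a 27-voxel neighbourhood, a 3.4 mm grid and assumed values of rho. FC and fALFF are not touched. ReHo is one of three imaging outcomes in a 15-person Praxis group, and the stated success targets (mean SUS score and session completion) do not use it.

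**What to change.** In *Neuroimaging changes following Praxis treatment*, state that ReHo is computed on the unsmoothed data after nuisance regression (step vii), and that the resulting ReHo map is smoothed at 5 mm FWHM before the mixed model. FC and fALFF may keep the present order. If the working pipeline already does this, one corrected sentence is enough.

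The cost is a change in the order of two steps for one measure. No new data are needed, and in the simulations the standardised contrast was no worse with the changed order.

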#### Relationships between neuroimaging changes and behavioral outcomes

Correlation analyses will be performed to examine the relationships between rs-fMRI findings and behavioral outcomes (from questionnaires and the Readiness Assessment Battery tasks: HAM-4-mTBI, modified version of the POWAR-TOTAL, 5-10-5 Shuttle Run, and 300-yard Shuttle Run), as well as clinical characteristics, with a significance threshold set at *p* < 0.05.

By comparing the behavioral outcomes from questionnaires and the Readiness Assessment Battery between baseline and post-rehabilitation, this study aims to identify any significant changes occurring between these assessment points. To compare between-group differences in behavioral outcomes, improvements during the 4-week intervention will be calculated by subtracting the baseline value (the first visit) from the post-rehabilitation value. A general linear model will be used to assess between-group differences in primary and secondary outcomes. Estimated marginal means, standard errors (SEs), 95% confidence intervals, and effect sizes will be reported for the outcomes derived from the general linear model. Effect sizes will be interpreted as small (0.01), medium (0.06), and large (0.14) (62). The Minimum Clinically Important Difference (MCID) will be calculated for all outcomes using the equation MCID = SD ^*^ 0.2.

#### Praxis scores as mediators of neuroimaging changes and behavioral outcomes

A mediation analysis will be conducted to explore whether Praxis scores (e.g., response times, accuracy, head velocity) mediate the relationship between rs-fMRI outcomes and behavioral outcomes. For all analyses, we will use the Praxis metrics that account for and remove the influence of game parameters (i.e., tailored treatments) selected by the Occupational Therapist. This analysis will follow a four-step regression-based approach:

Establish a significant association between rs-fMRI outcomes and behavioral outcomes.Verify a significant association between rs-fMRI outcomes and Praxis scores.Demonstrate that Praxis scores predict behavioral outcomes while controlling for rs-fMRI outcomes.Compare the direct effect of rs-fMRI outcomes on behavioral outcomes with its effect in the presence of Praxis scores. Bootstrapping will confirm the significance of the mediation effect.

By following this method, we will pinpoint the Praxis scores that significantly mediate the relationship between rs-fMRI outcomes (body structure and function impairments) and behavioral outcomes. Individual factors, such as demographic and personal factors, will also be considered. The findings will help formulate hypotheses and guide the design of future clinical studies to explore functional performance thresholds.

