#### Praxis performance as a marker of recovery (readiness for return to duty)

This study may provide insight into reasonable thresholds for RTD decisions based on behavioral outcomes and provide insights for future research on the role of Praxis-delivered augmented vestibular rehabilitation in recovery from mTBI. Accordingly, the team will conduct the following statistical analyses.

We propose that participants' performance on the Praxis system can serve as an indicator of their recovery from mTBI. The team aims to test this hypothesis by comparing longitudinal rehabilitation compliance scores with behavioral outcomes and self-reported symptom severity. At a broader population level, we anticipate that participants who exhibit the most significant increases in Praxis scores (metrics that account for and remove the influence of game parameters selected by the Occupational Therapist) will also show the most substantial improvements in their performance on the Readiness Assessment Battery and in self-reported symptom severity, as measured before and after the 4-week intervention. To validate this, we will use standard statistical methods to compare weekly Praxis performance metrics (calculated as the average outcomes for each session within a week). Additionally, we expect that day-to-day participation in Praxis will correlate with the overall recovery trajectory from mTBI. To examine this, we will compare longitudinal data collected from Praxis, specifically focusing on (A) daily Praxis performance metrics and (B) daily pre- and post-exercise VOMS symptom scores (38). To test the hypothesis that these measures are correlated within a session, we will employ methods such as first-differences regression to correct for directional biases and identify correlations in these longitudinal data points.

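### Game settings follow the participant's own performance and symptoms, so removing their influence from the Praxis scores can remove part or most of the recovery signal, depending on the method

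*Protocol article*

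**What the plan says.** Three parts of the protocol article bear on this.

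- **How settings are chosen** (*Four-week rehabilitation program*, *Praxis group*): "the Occupational Therapist will adjust visual/cognitive load, duration, and movement parameters (e.g., head velocity) based on patient performance and symptoms". Head velocity is the named example of a movement setting.
- **Which score is analysed** (*Praxis scores as mediators of neuroimaging changes and behavioral outcomes*): for every analysis, "we will use the Praxis metrics that account for and remove the influence of game parameters (i.e., tailored treatments) selected by the Occupational Therapist". The same section asks whether "Praxis scores (e.g., response times, accuracy, head velocity) mediate the relationship between rs-fMRI outcomes and behavioral outcomes", so head velocity is also a score.
- **What the score is used for** (*Praxis performance as a marker of recovery*): the proposal is that "performance on the Praxis system can serve as an indicator of their recovery from mTBI". The prediction is that "participants who exhibit the most significant increases in Praxis scores", again with the influence of settings removed, "will also show the most substantial improvements in their performance on the Readiness Assessment Battery and in self-reported symptom severity". Daily Praxis metrics are also set against "daily pre- and post-exercise VOMS symptom scores".

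The article does not say how the influence of settings is removed. Neither the weekly assessments, the follow-up assessment nor the treatment description mentions Praxis play at a setting common to all participants.

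**The concern.** Settings here are a response to the participant's state, not an outside nuisance. Someone who improves is likely to be moved to harder play; someone with more symptoms is likely to be eased. The settings therefore lie on the path between recovery and score. Subtracting an effect of settings that was estimated from those same sessions also subtracts some of the recovery that led to them.

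Head velocity shows this most clearly. If the setting defines the movement asked for, a participant who meets each new demand has little left in the head-velocity score once the setting is taken out.

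The daily symptom analysis has a related difficulty. Symptoms help to determine settings, and settings affect both the score and later symptoms.

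At stake is how a null result would be read. Praxis performance could be judged uninformative about recovery when the weak association came from the way the score was produced.

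**Working it through.** The article gives no figure for this analysis, so there is nothing to reproduce. The check is algebra plus an illustrative simulation.

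**Inputs from the article.** 15 Praxis participants; about 20 sessions (5 days × 4 weeks); settings driven by performance and symptoms.

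**Assumed model.** Score S = A − βD + e, where A is ability, D is difficulty and e is session noise. Next difficulty = current difficulty + k × last score + small noise. A larger k means faster tailoring.

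**Algebra.** Regressing S on D in the trial data estimates a slope of about −β + λ, where λ = Cov(A, D)/Var(D). Because difficulty follows ability, λ is positive. The adjusted change is then

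ΔS − (−β + λ)ΔD = ΔA − λΔD + Δe.

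If difficulty tracks ability perfectly (D = A/β), then λ = β and λΔD = ΔA: nothing is left but noise. If β is known from elsewhere, the adjusted change is ΔA + Δe and the signal stays whole. The unadjusted change is ΔA − βΔD + Δe, so the raw score is distorted as well.

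**Simulation.** All of these are assumptions: β = 1, noise SD 0.5, baseline ability SD 1, ability rising linearly over 20 sessions. Set A has ability gain mean 1, SD 0.7 and k from 0.1 to 0.6. Set B has gain mean 1.5, SD 1 and k from 0.1 to 0.9. The score change is the mean of week 4 minus the mean of week 1. Entries are average correlations with true gain.

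| Measure | Set A | Set B | Mean gain kept, set B |
|---|---|---|---|
| Raw score | 0.06–0.31 | 0.05–0.40 | 2–43% |
| Settings removed, pooled regression | 0.06–0.15 | 0.06–0.35 | 6–16% |
| Settings removed, within-person regression | about 0.62–0.75 | 0.50–0.84 | 35–49% |
| Settings removed, difficulty effect known | 0.86 | 0.92 | 100% |
| Change in achieved difficulty | 0.40–0.77 | not computed | not computed |
| Two single fixed-setting blocks (session 20 minus session 5) | about 0.60 | not computed | not computed |

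In set A, within-person regression kept 57–68% of the mean gain. Without tailoring (k = 0), every adjustment in set B gave 0.86–0.92 and kept 97–100%, so the loss comes from the feedback.

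**Closed-form check for set A.** Week 1 to week 4, like session 5 to session 20, spans 15 of the 19 steps. The SD of true change is therefore 0.7 × 15/19 = 0.553, variance 0.305.

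- Known difficulty effect, five-session means: noise variance 2 × 0.25/5 = 0.10; correlation √(0.305/0.405) = 0.87.
- Two single blocks: noise variance 2 × 0.25 = 0.50; correlation √(0.305/0.805) = 0.62.

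Sample correlations with 15 people average slightly lower, in line with 0.86 and 0.60.

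**The case against.** **The correction may be sound.** The article says that the influence of settings is removed, not how. A condensed article may leave the formula to the full protocol or analysis plan, so its absence is no finding. With an outside calibration nothing is lost, and within-person regression does far better than pooled. This stands. A reader might infer that removing the settings destroys the recovery signal, or that the marker hypothesis cannot be tested. The documents do not support that: the loss runs from almost none to almost all, according to a method that the article does not state.

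**The raw score would be no better.** This also stands. Wishing to correct for settings is right; the weak point is performance-driven settings with no described reference from which to learn the difficulty effect.

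**The reach is limited.** A reader might take Praxis scores to carry the whole trial. They do not. They belong to a secondary, exploratory aim. The usability target, session completion, pre-post tests, imaging change, between-group models and the return-to-duty thresholds taken from Control-group outcomes do not use them. The comparison of compliance with outcomes does not depend on the adjusted score either.

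**Safeguards exist.** The plan warns that Praxis performance may not correlate with improvement, and it uses first-differences regression for the daily data. The warning rests on the study being the first of its kind, not on adaptive settings. First differences remove stable differences between people, but not day-to-day feedback from symptoms to settings. That remaining bias was not quantified here.

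**A fixed block has its own faults.** It can hit floor or ceiling, it is open to game learning, and it must not override tailoring to symptoms. Two single blocks (0.60) correlate with true gain no better than within-person adjustment in set A. Their advantage is that they leave the mean gain unbiased, apart from learning, and put everyone on one scale.

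**Conclusion.** The concern holds in a bounded form. The settings are chosen from the same performance and symptoms that the Praxis-score analyses try to measure, so achieved difficulty carries recovery information: in the simulation its change tracked true gain at 0.40 to 0.77. Treating it only as something to remove discards that information. An adjustment estimated from tailored sessions can then remove part or most of the signal.

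The sizes show direction and range only. They rest on an assumed linear difficulty effect, assumed noise and assumed speed of tailoring, none of which the article gives. That no reference play takes place is read from the article's list of assessments; the full protocol may describe some.

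The matter should be settled before sessions are played, because a later analysis plan cannot recover reference data that were never recorded. It does not threaten the trial's other conclusions.

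**What to change.** 1. **Analyse achieved difficulty.** In the mediation and marker-of-recovery sections, report the difficulty level reached as its own progress measure beside the adjusted score. This needs no extra data collection if the chosen settings are logged, as the planned correction already requires.
2. **Calibrate the difficulty effect independently.** Estimate it from data not driven by the participant's own performance. One source is calibration outside the trial. The other is a short scored reference block at a common setting chosen by the sponsor, after familiarisation and at week ends, played only where the therapist judges it tolerable. It is a measurement step and leaves tailoring unchanged. Comparing it with tailored play on the same day largely cancels ability and so helps to isolate the effect of the setting. Use the calibrated or reference score in the mediation, weekly and daily analyses. If full documentation already describes such a calibration, a sentence in the article suffices.
3. **If neither is available,** use within-person rather than pooled adjustment, and state in advance that a null Praxis-score result may reflect the adaptive settings.

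Items 1 and 3 cost only wording and analysis time. The reference block costs a few minutes of tailored play per week, with possible floor or ceiling effects, some remaining game learning, and missing blocks where it is not tolerated.
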